### Randomisation

After obtaining informed consent patients will be randomised into one of the two treatment arms. Patients are randomised by a secure link to a central randomisation database. Randomisation will be stratified for stroke severity (NIHSS score <20 versus ≥20), for centre and for time of symptom onset (within 4.5 h of symptom onset versus beyond 4.5 h of symptom onset, but within 4.5 h of estimated time of BAO).

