### Statistical considerations

#### Power calculation

Assuming an absolute increase of 10% of favourable outcome at 90 days by additional IA therapy compared to optimal medical care alone, we calculated that 712 patients would be needed. This calculation was based on a type 1 error of 5%, a type 2 error of 20%, and a presumed incidence of the primary outcome event of 30% in the group treated with optimal medical care. This latter incidence was based on data of the BASICS registry study [2]. Based on these assumptions the trial would yield a risk ratio of 1.33 with a 95% confidence interval of 1.09 to 1.63, that is, a relative increase of 33% more patients with a favourable outcome with additional IA therapy. The sample size formula used originated from the standard work on clinical trials by SJ Pocock [15]. To account for potential dropout a target of 750 patients was set.

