#### Data analysis

Continuous data will be summarised with means and standard deviations. For count data percentages will be given.

The primary aim of the univariable analysis is to compare the proportion of patients with a favourable outcome at 90 days between the two treatment groups. For this purpose a risk ratio with corresponding 95% CI will be calculated. The analyses will be based on the intention-to-treat principle.

Multivariable analyses will only be carried out if important incomparability is detected between the two treatment groups. In that case risk ratios will be calculated that are adjusted for the variables that show baseline imbalance. To this end Poisson regression will be used, similar to that used in the BASICS registry study [2].

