### Monitoring

An independent DSMB will monitor the trial. For efficacy a symmetrical two-sided stopping rule will be used. The size of the trial is based on the assumption of a 10% absolute increase of the proportion of patients with a favourable outcome treated with additional IA therapy as compared with optimal medical care alone. If the observed benefit is ‘clearly’ larger or if optimal medical care appears to be better than additional IA therapy early termination of the trial may be recommended. A restricted procedure will be used with alpha equal to 0.05 and a power of 0.80 [16].

Safety will be monitored as follows. The BASICS registry observed that the risk of symptomatic intracranial haemorrhage (sICH) in patients treated with IA therapy was 14% (95% CI 10-18%) and 7% (95%CI 3-11%) in those treated with IVT only [2]. A more than two-fold excess of symptomatic intracranial haemorrhage in the group treated with additional IA therapy as compared with maximum supportive treatment may therefore be considered as problematic. However, symptomatic intracranial haemorrhage is a contributing component of the primary outcome and hence is weighed during monitoring of this outcome. A higher than expected sICH rate in the absence of a significant difference in functional outcome may therefore lead to a decision to put the trial on hold to analyse the reason for this higher sICH rate and the need to change treatment recommendations such a adjustments in the dose of thrombolytics used or the use of specific devises.

The BASICS Trial Office will put an active follow-up system into effect, such that for each patient 90-day follow-up data and those on the occurrence of symptomatic intracranial haemorrhage are obtained without delay. The first interim analysis will be performed at the moment the 3-month follow-up data are available on the first 10 patients randomised. Every 4 months thereafter the DSMB will be given the latest follow-up data and will advise the steering committee about the continuation of the trial based on these data. Thus a sequential monitoring process is installed based on the procedures described by Whitehead in 1997 [16]. For this purpose the program PEST 4 will be used. The recommendation on the continuation will be based on: (1) stopping rules as described above; and (2) the most recent information from medical literature or congresses in the field of cerebrovascular disease.

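### The primary risk ratio leaves out the factors used to stratify randomisation, and the imbalance-triggered adjustment rule is the one least likely to bring them in; pre-specified stratum adjustment would be a free gain in precision

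*Protocol article*

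**What the plan says.** Protocol article, Randomisation: "Randomisation will be stratified for stroke severity (NIHSS score <20 versus ≥20), for centre and for time of symptom onset". The onset factor separates patients treated within 4.5 h of first symptoms from those treated later but within 4.5 h of the estimated time of occlusion.

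Protocol article, Data analysis: the day-90 proportions with favourable outcome are compared in a univariable analysis, summarised by a risk ratio with 95% CI, by intention to treat. On covariates: "Multivariable analyses will only be carried out if important incomparability is detected between the two treatment groups". If that happens, "risk ratios will be calculated that are adjusted for the variables that show baseline imbalance", using Poisson regression. The section names no stratification factor.

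The NIHSS and onset-window strata do appear elsewhere. The Treatment and Objectives sections make them pre-specified subgroups for secondary analysis.

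**The concern.** The design and the analysis pull apart. Stratified randomisation removes chance differences between arms in the stratification factors. If these factors predict outcome, the treatment estimate varies less from trial to trial than a simple two-sample formula assumes. An analysis that ignores the strata therefore reports a standard error that is too large, an interval that is too wide and a test that is conservative.

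The adjustment rule does not repair this. It looks for imbalance, which the design has already suppressed in the strata, and so would mainly pick up other variables that differ by chance. What makes a covariate worth adjusting for is its prognostic strength, and the rule does not refer to it. The covariate set is also settled only after the arms have been compared.

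At stake are precision and some power in a trial where patients are scarce: the Trial status section reports 21 randomised between October 2011 and July 2013.

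**Working it through.** **Inputs from the Power calculation section.** Control rate 30%, absolute increase 10 points (so 40%, RR 4/3), type 1 error 5%, type 2 error 20%, 712 patients before dropout, expected 95% CI 1.09 to 1.63. Two-sided testing and 1:1 allocation are not stated there; both are assumed because they reproduce 712.

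**Inputs not in the article (assumed).** Stratum shares and outcome rates by stratum. I take two equal NIHSS strata, control rates that average 30%, a common RR of 4/3, and strata exactly balanced between arms.

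**1. Reproduce the plan's figures.**
- Per arm: n = [1.96·√(2·0.35·0.65) + 0.8416·√(0.3·0.7 + 0.4·0.6)]² / 0.10² = (1.3221 + 0.5646)² / 0.01 ≈ 355.9, so 356 per arm and 712 in total.
- Crude log-RR SE = √[0.7/(0.3·356) + 0.6/(0.4·356)] = √(0.006554 + 0.004213) = 0.1038.
- CI = 1.333·exp(±1.96·0.1038) = 1.09 to 1.63.

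Both stated figures reproduce. The stated interval is the crude, unstratified one.

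**2. Standard error that respects the strata (45% and 15%).** Only within-stratum variance counts.
- Control: 0.5·(0.45·0.55 + 0.15·0.85) = 0.1875.
- Treated (60% and 20%): 0.5·(0.60·0.40 + 0.20·0.80) = 0.2000.
- SE = √[0.1875/(356·0.30²) + 0.2000/(356·0.40²)] = √(0.005852 + 0.003511) = 0.0968.
- Crude/stratified = 0.1038/0.0968 = 1.07. Variance ratio = 0.009363/0.010768 = 0.87.
- Under the null the variance ratio is 0.1875/0.21 = 0.89.

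**3. Consequences in the same case.**
- Actual two-sided size of the crude test: 2·[1 − Φ(1.96/√0.893)] = 2·[1 − Φ(2.074)] ≈ 3.8%. Simulation gives 3.7%, against about 5% for the stratified analysis.
- Power, with ln(4/3) = 0.2877: crude Φ[(0.2877 − 1.96·0.1038)/0.0968] = 80.8%; stratified Φ[(0.2877 − 1.96·0.0968)/0.0968] = 84.4%. Simulation with the Mantel-Haenszel RR gives about 81% and 85%. The loss is about 4 points.

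**4. Range over the unknown gap (equal strata, 356 per arm, RR 4/3).**

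| Control rates | Stratified SE | Crude SE too large by | Stratified CI | Size of crude test | Power crude / stratified |
|---|---|---|---|---|---|
| 30% / 30% | 0.1038 | 0% | 1.09–1.63 | 5.0% | 79.2% / 79.2% |
| 40% / 20% | 0.1007 | 3% | 1.09–1.62 | 4.5% | 79.9% / 81.5% |
| 45% / 15% | 0.0968 | 7% | 1.10–1.61 | 3.8% | 80.8% / 84.4% |
| 50% / 10% | 0.0909 | 14% | 1.12–1.59 | 2.9% | 82.3% / 88.6% |

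Putting 60% of patients in the NIHSS ≥20 stratum changes little: at a 30-point gap the stratified SE is 0.0971, with power 80.7% and 84.2%. The 79.2% in the first row comes from the log-RR Wald test; the pooled test of proportions used for the sample size gives 80.0%.

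**5. Variance choice if Poisson regression is kept.** The model-based Poisson SE for a binary outcome is √[1/(0.3·356) + 1/(0.4·356)] = √(0.009363 + 0.007022) = 0.128, with CI 1.04 to 1.71. That is wider than the crude interval. The article does not say which variance its Poisson model would use.

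**The case against.** The strongest reply is that the plan is valid and consistent with itself. The sample size and expected CI are those of a crude comparison, a crude comparison is planned, and it delivers its 80% power. Ignoring the strata errs on the safe side. This stands, and it is why the point is an improvement and not a flaw in validity.

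Second, the size is not in the documents. The article gives no outcome rate or share by stratum and does not say how strongly the strata predict outcome. The calculation also assumes exact balance, which many small centres could weaken somewhat. This stands too; the result can only be given as a range that starts at zero.

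Three stronger readings do not hold.
- A reader might infer that the strata never enter the analysis. Two of them define pre-specified subgroups; they are only missing from the planned primary RR.
- A reader might infer that the crude and adjusted RRs compete as the trial result. The text does not say which prevails if both exist, but nothing says that the adjusted one replaces the univariable one. The more natural reading is a crude primary RR with a conditional supplementary model.
- A reader might infer that the false-positive rate is raised. Ignoring balanced strata lowers it.

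Nor is the matter simply left to an analysis plan. A threshold for important incomparability might be, but the article itself fixes the covariate strategy by allowing adjustment only on observed imbalance. A plan that adjusted for the strata regardless would contradict it.

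**Conclusion.** The point holds as a free improvement. The primary RR omits the factors on which randomisation is stratified, and the imbalance rule is poorly suited to bringing them in. If the strata are prognostic, the interval is conservative and power is lost; the trial's validity and sample size are not undermined.

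Under the central assumption (equal NIHSS strata, control rates 45% and 15%), the crude SE is about 7% too large and the CI bounds would move by 0.01 to 0.02. Gaps from 0 to 40 points put the power loss between 0 and about 6 points. These figures cover the NIHSS stratum only. A prognostic onset window would add a little: in simulation with 60% of patients at NIHSS ≥20 and a 30-point NIHSS gap, a further 10-point onset effect gave 81.9% crude against 85.7% stratified power.

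**What to change.** In Data analysis:
- Pre-specify as the primary estimate a risk ratio adjusted, whatever the observed balance, for the NIHSS stratum (or baseline NIHSS) and the symptom-onset stratum, with centre accounted for as a stratification factor where numbers allow.
- Name the estimator: a stratified Mantel-Haenszel RR, or Poisson regression with robust (sandwich) variance. Exclude model-based Poisson errors.
- Report the unadjusted RR as supportive.
- Delete the imbalance-triggered choice of covariates.

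The cost is wording. The factors are already recorded at randomisation, no extra data or patients are needed, and the sample size can stay as it is.

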### Safety reporting

An adverse event (AE) is any unfavourable and unintended sign, symptom, or disease occurring during the follow-up period of the study. Adverse events occurring after randomisation will be recorded on the adverse event page of the CRF. A serious adverse event (SAE) is defined as any adverse event that results in: (1) death; (2) a life-threatening condition; (3) inpatient hospitalisation or prolongation of existing hospitalisation; or (4) persistent or significant disability/incapacity.

Adverse reactions are all untoward and unintended responses to the investigational treatment related to any dose or device used.

Serious unexpected adverse reactions (SUSARs) are adverse reactions, of which the nature, or severity, is not consistent with the applicable product information.

All SAEs and SUSARS will be reported to and collected by the data coordination unit. An Internal Safety Committee will review safety data on an ongoing basis, including monitoring the trend in serious adverse outcome events and submitting reports to regulatory agencies and the data safety monitoring board (DSMB).

### Monitoring

An independent DSMB will monitor the trial. For efficacy a symmetrical two-sided stopping rule will be used. The size of the trial is based on the assumption of a 10% absolute increase of the proportion of patients with a favourable outcome treated with additional IA therapy as compared with optimal medical care alone. If the observed benefit is ‘clearly’ larger or if optimal medical care appears to be better than additional IA therapy early termination of the trial may be recommended. A restricted procedure will be used with alpha equal to 0.05 and a power of 0.80 [16].

Safety will be monitored as follows. The BASICS registry observed that the risk of symptomatic intracranial haemorrhage (sICH) in patients treated with IA therapy was 14% (95% CI 10-18%) and 7% (95%CI 3-11%) in those treated with IVT only [2]. A more than two-fold excess of symptomatic intracranial haemorrhage in the group treated with additional IA therapy as compared with maximum supportive treatment may therefore be considered as problematic. However, symptomatic intracranial haemorrhage is a contributing component of the primary outcome and hence is weighed during monitoring of this outcome. A higher than expected sICH rate in the absence of a significant difference in functional outcome may therefore lead to a decision to put the trial on hold to analyse the reason for this higher sICH rate and the need to change treatment recommendations such a adjustments in the dose of thrombolytics used or the use of specific devises.

The BASICS Trial Office will put an active follow-up system into effect, such that for each patient 90-day follow-up data and those on the occurrence of symptomatic intracranial haemorrhage are obtained without delay. The first interim analysis will be performed at the moment the 3-month follow-up data are available on the first 10 patients randomised. Every 4 months thereafter the DSMB will be given the latest follow-up data and will advise the steering committee about the continuation of the trial based on these data. Thus a sequential monitoring process is installed based on the procedures described by Whitehead in 1997 [16]. For this purpose the program PEST 4 will be used. The recommendation on the continuation will be based on: (1) stopping rules as described above; and (2) the most recent information from medical literature or congresses in the field of cerebrovascular disease.

### Ethical considerations

The study will be conducted according to the principles of the Declaration of Helsinki (http://www.wma.net21-10-2008) and in accordance with the Dutch Medical Research Involving Human Subjects Act (WMO). The BASICS trial was approved by the ethics committee of the St. Antonius Hospital on 20 January 2011 and is registered under number R-10.39A. National ethical approval was given by the Central Commission of Human Research (CCMO) on 21 December 2010 and is registered under number NL33550.100.10. Approval by the local medical ethical review board is required for each participating centre before start of patient inclusion.

Patients or their legal representatives will be informed about the trial by their treating neurologist or neurology resident who will also obtain informed consent. In acute situations or if the patient is incapable to give written informed consent oral informed consent may be obtained. In case of oral informed consent a witness (for example, family or nurse) should be present when the information is presented to the patient or patient representative. A written summary that describes the essential information will be presented to the patient or patient representative. The witness, and responsible neurologist or neurology resident will sign this document.

In case of a subject with severe decrease of consciousness (along with national legislations), informed consent can be obtained from the patient’s proxy in person or by telephone as long as the identity of the proxy can be confirmed. If approved by the local ethical review board an independent physician can sign informed consent. Community hospitals are encouraged to obtain informed preliminary consent for trial participation of the subject or his proxy prior to transfer.

In patients who are not eligible for standard IVT because IVT cannot be initiated within 4.5 h of symptom onset but who are treated within 4.5 h of estimated time of BAO informed consent has to be obtained prior to IVT. In those centres where CTA or MRA is not part of the standard acute stroke work-up informed consent has to be obtained prior to CTA or MRA.

### Publication of the trial results

The trial results will be published by the members of the Executive and Steering Committee, on behalf of the investigators.

## Discussion

There are several factors that distinguish patients with BAO from those with middle cerebral artery (MCA) occlusion that may warrant a different treatment approach:

*Severity of deficit:* previous studies have suggested a greater benefit of IA therapy in patients with a severe deficit.

*High poor outcome rate:* because of a higher poor outcome rate, patients with BAO have more to gain.

*Collateral flow:* the basilar artery not only receives collateral flow through cortical cerebellar branches, comparable to the cortical hemispheric branches of the MCA, but also by retrograde filling by the anterior circulation through the posterior communicating arteries as part of the circle of Willis. IVT may be more effective in the presence of good collateral flow, by attacking the thrombus from both sides.

*Time window for treatment:* the BASICS registry data suggest the presence of a longer time window from symptom onset to time of treatment. The PROACT studies used a limit of time from symptom onset to time of treatment of 6 h [4,17]. The IMS III study used a 5-h time window from symptom onset to initiation of IAT [18]. The BASICS trial uses a 6-h time window from estimated time of BAO to initiation of IA treatment. The BASICS registry used the estimated time of symptom onset consistent with the clinical diagnosis of BAO to treatment rather than the more commonly used time of onset of any symptoms to treatment. Previous studies have shown that BAO is preceded by prodromal symptoms in >60% of patients [19,20]. Most of these patients would be excluded from a potential trial using the time of onset of first symptom <4.5 h to treatment as an inclusion criterion. We believe that the results from the BASICS registry support the use of the estimated time of BAO rather than using the time of onset of any symptom to treatment as an inclusion criterion for the BASICS trial.

*IVT* versus *IVT/IAT comparison:* IV thrombolysis is the current standard of care in patients presenting with acute ischaemic stroke with a proven safety and efficacy and therefore should be regarded as the current ‘Gold Standard’ with which potential new treatment strategies should be compared.

The use of an IVT only arm in a trial of patients with acute symptomatic BAO is supported by the results of the BASICS registry in which no significant difference was found between IVT or IAT treated patients with a severe deficit [2].

The performance of a trial comparing IVT alone vs. IAT alone in patients with BAO does not seem feasible nor ethical. Referral of a patient to an intervention centre for randomisation between IVT vs. IAT alone would mean delaying the initiation of a treatment which is of proven benefit - whereas there is convincing evidence for the principle of ‘time is brain’, also in patients with BAO [21,22]. The number of patients with BAO presenting directly to an intervention centre will be too limited. Patients with BAO only represent an approximate 5% of all IVT eligible patients, and only 40% of patients in the BASICS registry where admitted directly (without referral) to an intervention centre.

In order to include a sufficient number of patients the BASICS trial will therefore mainly depend on the inclusion of patients referred from non-intervention community hospitals. The non-intervention hospitals are encouraged to start IVT without delay before sending the patient with the clinical diagnosis of BAO to the intervention centre.

A combined IV and IA approach to acute ischaemic stroke therapy was designed to offer rapid initiation of IV rt-PA, followed by additional titrated local IA therapy, to patients with moderate-to-severe strokes (NIHSS ≥10). The goal was to achieve higher rates of early, successful reperfusion in a widely accessible manner. This approach has been tested in clinical trials of >200 patients, starting with the Emergency Management of Stroke (EMS) pilot trial from 1995 to 1996, followed by the Interventional Management of Stroke (IMS) I trial in 2001, the IMS II trial from 2003 to 2006, and several additional cohorts [23-25]. The data from EMS and IMS show that the combined approach to recanalisation may be more effective than standard IV rt-PA alone for moderate-to-severe (NIHSS ≥10) strokes, while maintaining a similar safety profile. The recently published IMS III trial data did not show a significant difference in outcome comparing IV rt-PA with IV rt-PA followed by IAT in patients with a NIHSS of 8 or greater treated within 3 h [26]. Few patients with BAO were included, about 2% in both treatment arms. Furthermore, few patients had radiologic confirmation of occlusion and most patients in the IA arm were treated with IA thrombolysis or first generation thrombectomy devices, much less effective than the currently used stentretrievers [27,28].

### IVT arm

The 4.5-h time window is based on the results of the ECASS III study [7]. A time window of 0–4.5 h from symptom onset to treatment in patients with acute ischaemic stroke is widely accepted. The BASICS registry results show the safety of using a 0 to 4.5-h time window from estimated time of occlusion to treatment in patients with acute BAO [2].

### IVT + IAT arm

Based on the results of the PROACT studies the 6-h time window for IA thrombolysis in patients with MCA occlusion is widely accepted [4,17].

A case series of 69 patients treated with IA thrombolysis (urokinase, reteplase or alteplase) following full dose IVT showed the safety of full dose IVT followed by IA thrombolysis. Symptomatic haemorrhage occurred in four out of 69 (5.8%) patients [29].

The MERCI studies suggested safety of mechanical thrombectomy up to 8 h from symptom onset [30]. The BASICS study shows that a time window of 0 to 6 h from estimated time of occlusion to IA treatment is safe in patients with a severe deficit while little can be gained in both IVT and IAT treated patients beyond the 6-h time window [2].

The main theoretical advantage of an IA approach is the variety of treatment options, which can be tailored to the individual patient. Because of the variety in approved IA treatment options and the limited number of patients, the experience with specific devices or thrombolytics varies considerably among stroke centres both within and between countries. Limiting the use of treatment options would exclude centres from participation because of lack of experience with the selected device or thrombolytic despite ample experience in the use of alternative devices or thrombolytics. New devices or thrombolytics that become available during the study may be used in the IAT arm depending on national and local approval and experience. Prior approval by the steering committee needs to be obtained.

